## Abstract

**Background::**

Cutaneous leishmaniasis (CL) is a skin neglected tropical disease, with an estimated 40,000 new cases each year in Ethiopia. CL causes ulcers, nodules, and plaques on the skin, and in some instances the destruction of the nasopharyngeal mucosa and cartilage. Some CL lesions may heal spontaneously, whilst other lesions may require therapies which are associated with discomfort, adverse effects, prolonged treatment, and a frequent lack of a complete response. Scarring, a sequela of CL, causes permanent disfigurement and is associated with stigma linked with a reduction in health-related quality of life.

The choice of treatment for CL is based upon factors including the causative species; the number, extent, size, and location of lesions; and the availability of treatments. The development of robust evidence for CL treatment is hindered by a lack of validated and appropriate outcome measures and few data to support hypothesis-generation and trial design. There is a paucity of prospective data with well-defined treatment outcomes for CL caused by
*L. aethiopica*.

**Aim::**

The overall aim of this study is to improve the understanding of the health and economic burden of CL.

**Methods::**

We have designed an observational, multi-centre cohort study to examine treatment outcomes for CL in Ethiopia which includes clinical outcomes, laboratory outcomes, patient reported outcome measures, scar assessments and cost effectiveness. We aim to recruit up to 750 participants across two hospital sites. We present here the protocol for this cohort study with a 12-month follow up period for each participant.

**Conclusions::**

These data will inform the design of randomized controlled trials to evaluate new treatment strategies, with appropriate economic evaluations. This will help improve evidence-based guidelines and support evidence-led policy decisions, not only in Ethiopia but also globally.

## Introduction

Up to a million new cases of cutaneous leishmaniasis (CL) occur each year, primarily in the world’s poorest communities
^
1
^. CL is the most common form of leishmaniasis, which is caused by infection with protozoa of the genus Leishmania, acquired via the bite of a female phlebotomine sandfly. Infection leads to the development of ulcers, nodules, and plaques on the skin. Depending on the infecting
*Leishmania* species, spontaneous resolution of infection can take many months or years and medical therapies are associated with discomfort, adverse effects, prolonged treatment, and a frequent lack of complete response (
World Health Organization). Lesions often heal with lifelong scarring or destruction of the nasopharyngeal mucosa causing permanent disfigurement, and associated stigma, and overall psychological morbidity, contributing to a reduction in health-related quality of life (HRQoL)
^
2
^. These multidimensional morbidities and the often-arduous process of treatment-seeking also impose a substantial economic burden in terms of both costs of care and income loss, which can exacerbate the stress and social impact associated with CL and inhibit access to care
^
3–
5
^.

The choice of treatment for CL is based upon several factors including the causative species; the number, extent, size and location of lesions; and the availability of treatments. Small lesions not located near a joint or facial structure may be allowed to self-heal or be treated with a topical agent, intra-lesional injection, cryotherapy, or heat therapy. Localised treatments for CL are associated with irritation, pain, discomfort, and in the case of cryotherapy, long-term skin changes
^
6
^. Large or widespread lesions and those involving the mucosa require systemic treatment
^
7,
8
^. Despite the large number of cases of CL each year, the evidence for determining the best treatment modality remains limited.

In Ethiopia, CL is a growing public health problem, with an estimated 40,000 new cases each year. Several
*Leishmania* species cause CL in Ethiopia; most infections are thought to be due to
*L. aethiopica*
^
9
^, but
*L. donovani*,
*L. major* and
*L. tropica* are also present.
*L. aethiopica* is associated with three distinct clinical forms of CL; localised CL (LCL); mucocutaneous leishmaniasis (MCL); and diffuse CL (DCL), which is the most disfiguring and difficult to treat
^
9
^. Lesions caused by
*L. aethiopica* most commonly occur on the face
^
10
^. The diverse range of clinical phenotypes and presentations makes early diagnosis by community-based health workers difficult. Standard CL treatment in Ethiopia is with intralesional or parenteral sodium stibogluconate (SSG), which may be combined with cryotherapy using liquid nitrogen. There is a particular paucity of prospective data with well-defined treatment outcomes for CL caused by
*L. aethiopica*. A systematic review of treatment for CL caused by
*L. aethiopica* identified two randomised trials with a total of 26 participants and two prospective, non-randomised studies
^
11
^. All four studies were assessed to have methodological limitations by the authors. One of the small, randomised trials compared itraconazole with placebo (n=14 participants)
^
12
^ and the other compared rifampicin, isoniazid and amithiozone with pentamidine (n=12 participants)
^
13
^. The much larger prospective study reported improvement in various forms of CL: 81% of participants improved with liquid nitrogen cryotherapy and 85% improved with intramuscular SSG (20 mg/kg up to a maximum of 850mg daily) for 30 days
^
14
^. Another study reported that 21% of participants had “a positive outcome” with intralesional pentavalent antimonial drug meglumine antimoniate (MA) and 47% had “a positive outcome” with systemic MA (20 mg/kg)
^
15
^.

The development of robust evidence for CL treatment is hindered by a lack of validated and appropriate outcome measures and few data to support hypothesis-generation and trial design. A Cochrane review demonstrated that existing studies used heterogeneous outcome measures which mostly lacked validity, hindering comparison of study results
^
16
^. A consensus document on “harmonized” clinical research methodologies for LCL (but not MCL or DCL) was published by an international group of experts following meetings organised by WHO and the Drugs for Neglected Diseases initiative
^
17
^. This publication highlighted the importance of laboratory confirmation with identification of
*Leishmania* species in future trials and defined “initial” cure for non-American CL as more than 50% re-epithelialization (if an ulcer) or flattening (if a non-ulcerated lesion) at Day 42; and as 100% re-epithelialization or flattening at Day 90. “Final” cure was defined as 100% re-epithelialization or flattening at Day 180. More recently, open label studies, incorporating these expert-agreed outcomes, were conducted on treatment for CL due to
*L. aethiopica*. One study reported physician-determined cure rates of 59.7% for intralesional SSG
^
18
^ at Day 90, whilst another study reported physician-determined cure rates of 12.5% and 72.7% for miltefosine
^
19
^ at two study sites at Day 90.

The “harmonized” clinical research methodologies for LCL provided a significant step forward but several gaps remain. No agreed methodologies are available for assessing flattening or re-epithelisation and it remains unclear if outcomes should be measured from the start or end of a course of treatment. The agreed outcome measures are entirely clinical and do not include measures to reflect the outcomes and experiences of affected individuals. The treatment preferences of individuals may be influenced by the frequency of adverse events and the extent to which healing improves their health and psychosocial wellbeing. Appropriate patient reported outcome measures (PROMs) therefore need to be identified and collected alongside clinical measures. Finally, the consensus document recognised that scarring should be assessed as a long-term outcome but did not propose a method for doing so.

Given the scarcity of resources for health, and for the treatment of CL in particular, treatment recommendations should also be informed by an understanding of costs and efficiency. However, cost-effectiveness analyses of alternative treatment strategies for non-American CL have only been conducted in Asia
^
20–
23
^, none have addressed infection with
*L. aethiopica*, and only one has assessed effectiveness using a multidimensional outcome metric
^
20
^, which is essential for comparing the value of investments across intervention types and diseases. No studies of the economic burden of CL or treatment costs in Africa have been published. 

The Ethiopian Federal Ministry of Health (FMOH) has identified an urgent need for the evaluation of treatments alternatives for all forms of CL. Such evaluation requires better understanding of outcomes, and cost-effectiveness data. We therefore designed an observational, multi-centre cohort study of CL in Ethiopia
^
24
^.

## Aims & objectives

The overall aim of this study is to improve the understanding of the health, psychosocial and economic burden of CL, and to lay the groundwork for well-designed, randomized controlled trials and economic evaluations of alternative CL treatments in Ethiopia.

### Objectives

1.To assess clinical outcomes in LCL, MCL and DCL in a prospective cohort 2.To assess clinical parameters in LCL, MCL and DCL in a prospective cohort 3.To assess the change in HRQoL associated with CL before and after treatment.4.To develop a severity scale for CL5.To understand the lived experiences of individuals with CL attending a referral centre by conducting in-depth interviews6.To assess household costs of CL, health care provider and societal costs of treating CL7.To characterise how cell-mediated immune responses associate with treatment responses in CL due to L. aethiopica and Human Leucocyte Antigen (HLA) variation correlate with different clinical phenotypes.

## Methods

### Patient and Public Involvement

Patients with CL were involved in the validation of the translations of PROMs through focus group discussions, cultural adaptation and piloting.

### Study context

The study will enrol individuals receiving treatment for CL at two centres: ALERT Hospital, Addis Ababa and Boru Meda Hospital, South Wollo Zone, Amhara Region. ALERT Hospital serves as both a general hospital for patients in Addis Ababa and a regional and national specialized referral centre for individuals with CL and other skin conditions. The hospital has nine dermatologists and a 20-bed unit for the care of patients with CL and diagnoses approximately 1000 cases of CL managed on an inpatient or outpatient basis each year. Boru Meda serves as the general hospital and specialised referral service for all skin conditions in South Wollo zone. It has two dermatologists, and a 35-bed unit for the management of CL and diagnoses around 700 cases of CL, managed on an inpatient or outpatient basis each year.

### Timelines

Study recruitment began in April 2022 and is expected to continue until the sample size is reached or until the cut-off of September 30th, 2023, whichever occurs first. Follow-up is therefore expected to be completed by September 30th, 2024.

### Study participants and management

Adults and children with CL who are managed as inpatients or outpatients are eligible to participate in the study.

Inclusion Criteria: Participants with laboratory confirmed CL

Exclusion Criteria: Participants who have previously been treated with systemic anti-leishmanial therapy

Participants will be treated using the standard of care for CL at the centre where they are managed and in accordance with the Ethiopian national guideline
^
24
^ which will be agreed by two clinicians in consultation with the affected individual prior to enrolment. The treatment may be changed if deemed clinically appropriate. In general, if the size of the skin lesion is 4cm in diameter of smaller and not near a mucosal site the first line treatment is most frequently local therapy (cryotherapy and/or intralesional SSG). In general, if the diameter of the skin lesion is greater than 4 cm and/or near or involving a mucosal surface the initial therapy is usually intramuscular SSG for 28 days with or without adjunctive cryotherapy. Participants will be assessed on day 42 and further local or systemic therapy may be offered depending on the degree of clinical response.

We will classify CL using the operational definitions shown in
Box 1.

Box 1. Operational definitions of Cutaneous Leishmaniasis (CL)•    CL is diagnosed in a person with skin and/or mucosal lesions with evidence of
*Leishmania* infection in the affected tissues characterised by the presence of
*Leishmania* amastigotes on smear microscopy or growth of
*Leishmania* promastigotes in culture or the detection of
*Leishmania* DNA by polymerase chain reaction.•    Localized CL: A confirmed case of leishmaniasis, with no mucosal involvement, characterized by ten or fewer cutaneous papules and/or nodules and/or plaques with or without ulceration involving one body site•    Multi-regional localized CL: A confirmed case of leishmaniasis, with no mucosal involvement, characterized by ten or fewer cutaneous papules and/or nodules and/or plaques with or without ulceration involving two or more body sites•    Mucocutaneous leishmaniasis: A confirmed case of leishmaniasis characterized by ten or fewer papules and/or nodules and/or plaques with or without ulceration involving skin and an adjacent mucosal surface•    Mucosal leishmaniasis: A confirmed case of leishmaniasis characterized by papules and/or nodules and/or plaques with or without ulceration involving exclusively a mucosal surface•    Diffuse CL: A confirmed case of leishmaniasis characterized by eleven or more papules and/or nodules and/or plaques with or without mucosal involvement.Body sites are classified as:1. Head and neck2. Torso - anterior (including genitalia)3. Torso - posterior (including buttocks)4. Right upper limb5. Left upper limb6. Right lower limb7. Left lower limb 

### Overview of data collection

Study visits for data collection are scheduled at day 1, 14, 28, 42, 90, 180 and 360 (
Table 1). Treatment will be decided by the treating clinicians, who may or may not be one of the study dermatologists. All study specific data collection will be undertaken by a member of the study team. At the baseline visit, we will collect socio-demographic data, perform clinical assessment, and collect data on PROMs and costs. Follow-up data will be collected for all patients at specified time points, as detailed further below. In a subset of patients, additional biological samples will be collected for immunological and genetic studies. A further subset of participants will be selected for in-depth interviews.

**Table 1. T1:** Timetable of planned reviews and activities.. PSOAS-2: Patient and Observer Scar Assessment Scale version 2; DLQI: Dermatology Life Quality Index; CDLQI: Children’s Dermatology Life Quality Index; CLIQ: Cutaneous Leishmaniasis Impact Questionnaire; HLA: Human Leucocyte Antigen; PCR: polymerase chain reaction

	Day 1 (before 1 ^st^ treatment)	Day 14	Day 28 (end of 1 ^st^ cycle of systemic treatment)	Day 42	Day 90	Day 180	Day 360
**Participant and physician assessment of change**		X	X	X	X	X	
**Adverse reaction monitoring (if on treatment)**		X	X	X	X		
**Pain assessment**	X	X	X				
**Test of cure (if not healed)**					X		
**Scar assessment (PSOAS-2)**				X	X	X	X
**DLQI/CDLQI**	X	X	X	X	X	X	
**EQ-5D-5L**	X	X	X	X	X	X	X
**SF36**	X			X	X	X	X
**CLIQ**	X			X	X	X	
**Household costs**	X	X	X	X	X	X	X
**Immunological studies blood sample (subset)**	X		X		X		
**HLA typing blood sample**	X						
**Slit-skin smear for PCR**	X				X		
**Skin biopsy (subset of adults only)**	X				X		
**Digital image**	X	X	X	X	X	X	X

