### Clinical data

At the baseline visit, we will record the clinical phenotype of CL including the number, size, morphology
^
25
^ and location of lesions. Lesion dimensions (defined as the largest diameter of the lesion) will be measured using a disposable tape measure. Individuals with more than one lesion will be asked to indicate the lesion causing greatest concern and this will be designated the “index” lesion. Individuals may indicate two or more lesions of equal concern. In those with mucosal involvement, mucosal signs and symptoms are recorded. Clinicians will then provide a subjective global assessment of CL severity using a 3-point Likert scale (mild, moderate, severe). Slit-skin smears will be collected at baseline for microscopy and species identification using polymerase chain reaction (PCR).

At each follow-up visit, we will assess lesions for the degree of re-epithelization or flattening. For those with DCL, the number of resolved lesions and percent of lesions flattened per region is recorded. Clinicians will provide a global assessment of the improvement or worsening of CL using a 5-point Likert scale (worse, no change, minor improvement, major improvement, cure). At each visit, we will record the treatment being administered and any changes since the last visit. The adverse reactions to CL treatments will be assessed including the nature and severity of the reaction, the action taken, the presumed cause and the outcome. The Common Terminology Criteria for Adverse Events (CTCAE) version 5.0 will be used for describing adverse reactions and grading their severity. Slit-skin smear samples will be collected at day 90 for test of cure if the skin lesion is not healed.

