### Data analysis

**
*
Objective 1: To assess clinical outcomes in LCL, MCL and DCL in a prospective cohort.*
**

The primary outcome is the proportion of individuals with a healed index lesion by study day 90. In line with the consensus document on clinical trial outcomes cure will be defined as 100% re-epithelialization or flattening of the index lesion. Pre-specified additional outcomes are the proportion healed at day 42 and 180. Secondary outcomes include the frequency of adverse events and measures of HRQoL life.

There are no pre-existing high-quality data on cure rates for CL caused by
*L. aethiopica*. We calculated the sample size required to measure a range of cure-rates at 90 days with varying degrees of precision (
Table 2). Based on this we aimed to recruit up to 250 participants with each CL phenotype (LCL, MCL, and DCL) across the two sites. We anticipate that mucosal leishmaniasis will be rare and will recruit as many individuals with this type of disease as possible.

**Table 2. T2:** Sample sizes required to detect a range of cure rates with varying precision at day 90.

**Sample size**		**Percentage cured at 90 days**			
		50	60	70	80
	50	±13.1	±13.6	±12.7	±11.1
	100	±9.8	±9.6	±9.0	±7.8
	150	±8.0	±7.8	±7.3	±6.4
	200	±6.9	±6.8	±6.4	±5.5
	250	±6.2	±6.1	±5.7	±5.0

**
*
Objective 2: To assess clinical parameters in LCL, MCL and DCL in a prospective cohort.*
**

We will use descriptive statistics (means, medians, and proportions) to describe demographics and baseline characteristics of the cohort. In exploratory analysis, we will use univariable logistic regression to examine clinical and demographic variables associated with resolution of CL at Day 42, 90, and 180. Whilst not formally powered for these analyses, the findings will be viewed as hypothesis-generating and potentially form the basis for future studies.

**
*
Objective 3: To assess the change in HRQoL associated with CL before and after treatment.*
**

Changes in general, skin and CL-specific HRQoL will be assessed using the following PROMs: EQ-5D-5L, SF-36, DLQI/ CDLQI and CLIQ applied at the timepoints shown in
Table 1, and compared with clinical outcomes to determine validity and responsiveness.

**
*
Objective 4: To develop a severity scale for CL.*
**

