## Discussion

CL represents a major public health, psychosocial and economic problem both in Ethiopia and in the tropical – subtropical regions. A key target of the 2021-2030 WHO Neglected Tropical Diseases roadmap is a significant increase in the proportion of individuals with CL who are diagnosed and receive appropriate treatment. The 2021-25 Ethiopian strategic plan for Neglected Tropical Diseases, aims to meet the 2030 global target by increasing CL treatment centres from 14 to 30, diagnostic centres from 25 to 170 and to be able to detect 85% of cases and treat 95% of these. A better understanding of strategies to improve accessibility and treatment outcomes is a priority action to achieve this goal
^
28
^.

There are currently few prospective data of well-defined treatment outcomes for individuals with CL caused by
*L. aethiopica*, and no data on PROMs or costs. A large cohort of participants with CL will generate robust data on how outcomes are associated with key clinical characteristics such as lesion size, site and number. This will allow us to gain insights into expected clinical outcomes up to one year following treatment and accurately quantify the burden of adverse reactions associated with current treatments. There are new agents and combination therapies proposed for the treatment of leishmaniasis and our data will be valuable in helping design future trials of these approaches in individuals with
*L. aethiopica*.

This prospective cohort study will generate the most comprehensive and holistic dataset of CL, combining clinician determined and patient reported outcomes alongside health economic and laboratory data to better capture the impact of CL for affected individuals, their families, and communities. These data will inform the design of randomised trials to evaluate new treatment strategies, help improve evidence-based guidelines and support evidence-led policy decisions.

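### Table 1 limits adverse-reaction monitoring to participants on treatment and ends it at Day 90, while the Clinical data text sets neither limit; applied as written, Table 1 can miss reactions

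*Protocol article*

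**What the plan says.** All references are to the protocol article.

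- **Overview of data collection.** The visit schedule is: "Study visits for data collection are scheduled at day 1, 14, 28, 42, 90, 180 and 360". In Table 1 the row "Adverse reaction monitoring (if on treatment" is marked at Days 14, 28, 42 and 90, with no mark at Day 180 or Day 360.
- **Study participants and management.** For larger lesions or those near a mucosal surface, "the initial therapy is usually intramuscular SSG for 28 days with or without adjunctive cryotherapy". Later treatment is left open: "Participants will be assessed on day 42 and further local or systemic therapy may be offered depending on the degree of clinical response". Also: "The treatment may be changed if deemed clinically appropriate". Neither sentence gives an end date.
- **Clinical data.** "At each visit, we will record the treatment being administered and any changes since the last visit". The text then says that reactions to CL treatment will be assessed: what the reaction was, how severe, what was done about it, its likely cause and how it ended. It attaches no on-treatment condition and no last day.
- **Data analysis, Objective 1.** "Secondary outcomes include the frequency of adverse events".
- **Discussion.** The data are expected to "accurately quantify the burden of adverse reactions associated with current treatments".

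**The concern.** The article gives two collection rules for one secondary outcome, and the narrower one stands in the visit schedule that site staff are likely to work from. Under that rule, whether a participant is asked about reactions depends on still being treated on the day of the visit. Stopping treatment is one possible consequence of a reaction, so being asked can depend on the outcome being measured. The rule also fits poorly with treatment that may be given again from Day 42 and changed at any time.

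At stake is the adverse-event frequency, which could come out too low. The Discussion presents these data as an accurate measure of burden and as input to the design of later trials.

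**Working it through.** The plan states no figure to reproduce here. The check is schedule arithmetic.

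**Inputs**
- Visits with adverse-reaction monitoring: Days 14, 28, 42, 90 (Table 1).
- First systemic course: usually 28 days (Study participants and management), so Day 1 to Day 28.
- Further therapy: possible from the Day 42 assessment, with no end date (same section).
- Length L of a second course: not given. **Assumption:** L = 28 days, as for the first systemic course. Further therapy may also be local, and then this length need not apply.

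**Formulas.** A course started on day s ends on day s + L − 1 = s + 27. On the literal reading, it is monitored at a marked visit v if s < v ≤ s + 27. The share of the course seen by the last such visit is (v − s + 1)/28.

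**Literal reading of Table 1**

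| Start of course | End | Marked visits on treatment after the start | Share seen |
|---|---|---|---|
| Day 1 | Day 28 | 14 and 28 | 28/28 = 100% |
| Day 42 | Day 69 | none (Day 90 is 21 days later) | 0% |
| Day 62 | Day 89 | none | 0% |
| Day 63 | Day 90 | 90 | 28/28 = 100% |
| Day 70 | Day 97 | 90 | 21/28 = 75% |
| Day 80 | Day 107 | 90 | 11/28 = 39% |
| Day 91 or later | Day 118 or later | none | 0% |

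So a 28-day course started on any of Days 42 to 62 has no on-treatment monitoring visit after it begins. For these courses the loss comes from the on-treatment condition; the Day 90 end-point matters only for courses that run past Day 90.

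**With look-back to the previous visit.** At Day 90, a course started on Days 42 to 63 is fully covered (63 + 27 = 90). One started on Day 70 is 75% covered, on Day 80 39%, and after Day 90 not at all. Marking Days 180 and 360 as well covers the remainder of courses that run past Day 90, and later courses that end by Day 360.

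**Stopping between visits.** A participant who stops on Day 20 is off treatment at Day 28 and falls outside the row. The reaction is lost only if it was not recorded at Day 14 and is not asked about later.

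**Illustration only.** Let p be the true frequency and q the share of those with a reaction who are never asked while eligible under the row. The recorded frequency is p(1 − q). With p = 20% (assumed) and q = 10%, 25% or 50% (assumed), it is 18%, 15% or 10%. No value of p or q comes from the documents.

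**The case against.** The strongest reply is that the row label is shorthand and the Clinical data text governs. That text records treatment changes since the previous visit, so a stop between visits is noted. Its items on the action taken and the outcome of a reaction fit a participant who has already stopped. Table 1 itself sits awkwardly with a strict reading: Day 28 is headed as the end of the first systemic cycle, yet the row is also marked at Day 42, when many such participants would be off treatment. Continuing local therapy could explain that mark, so it does not settle the matter. The article is also condensed, and the recall wording of the form may be in a fuller document.

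This reply stands to the extent that loss is possible, not certain. It does not remove the conflict. The condition and the four marks are stated rules, and nothing says which rule prevails. Nor does the look-back reading supply a mark in Table 1 after Day 90.

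A reader might infer more than the documents support:
- *That these reactions are missed.* This holds only if Table 1 overrides the Clinical data text.
- *That the worse the reaction, the less likely it is to be recorded.* Nothing shows how severity relates to stopping, and a reaction recorded before the stop is kept.
- *That a second course has no coverage.* Its length, start and route are not given, and a 28-day course started on Days 63 to 89 does meet the Day 90 visit.
- *That treatment follows the Day 90 test of cure.* The article schedules the smear for unhealed lesions but does not say what follows. Later treatment is possible, but how common it is cannot be told.
- *That the use of both adverse events and adverse reactions is a second defect.* It is loose wording. The denominator for each treatment is analysis-plan detail.

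**Conclusion.** The point holds in conditional form: Table 1 and the Clinical data section give different rules for collecting a named secondary outcome. If Table 1 is followed literally, reactions can go unrecorded in participants who stop between visits without an earlier record, in second courses that fall wholly between Days 42 and 90, and in treatment begun after Day 90. Any resulting bias in frequency would be downward.

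The Day 42 to 62 window rests on an assumed 28-day second course. The size of the bias cannot be estimated, because the documents give no reaction rate, no stopping rate and no rate of retreatment. The point is worth correcting because the change is small, and the claim of accurate quantification depends on it. It concerns data collection only and implies nothing about how participants should be treated.

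**What to change.** Change the condition on the Table 1 row so that it applies if any CL treatment was received since the previous visit, and have the form ask about the whole interval. Mark the row also at Day 180 and Day 360 for participants treated since the visit before. Bring the Clinical data section into line by stating the same condition and the same last visit.

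Both later visits already take place, so the cost is a changed form instruction, slightly more data collection, and longer recall: up to 90 days at Day 180 (180 − 90) and 180 days at Day 360 (360 − 180). Mild reactions may be under-reported over such intervals, which should be acknowledged when the frequency is reported.
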